### Outcomes: measurement

#### Readmission data

The Discharge Abstract Database (DAD) is managed by the Canadian Institute for Health Information. The DAD contains demographic, diagnostic, procedural and hospitalization data on hospital discharges (i.e., inpatient, acute, chronic, rehabilitation) and day surgeries in Canada. Data in the DAD can be used to identify dates of index hospital admissions and, subsequently, readmissions. A subset of the DAD relating to Ontario hospital admissions is held at the Institute for Clinical Evaluative Sciences (ICES) in Toronto, Ontario. ICES is an independent, non-profit organization with a core mission to conduct research that contributes to the effectiveness, quality, equity and efficiency of health care and health services in Ontario.

To develop a data file of hospital readmissions among patients discharged from CTTs participating in the SCRIPT Programme, we will use information in the DAD to establish a link between patients and the team that treated them. The key to using this method successfully lies in our identification of a patient's most-responsible physician. In Ontario, all practicing physicians are required to register with the province's regulatory body, the College of Physicians and Surgeons of Ontario (the CPSO). The CPSO assigns every registered physician a unique registration number. This number is a data field in the DAD; it appears on a discharged patient's record line. It is also publicly available with the physician's name on the Internet site of the CPSO.

Leaders of GIM divisions will provide us with the names and team assignments of physicians who were on rotation in GIM CTTs during SCRIPT's intervention periods. When we know a physician's name from GIM records, we can search for his or her profile in the CPSO Internet site. Physicians' CPSO registration numbers will serve as the link between their positions in GIM CTTs and discharge information in the DAD. We will compile a list of registration numbers of physicians who served in GIM during the study period, submit the list to database managers at ICES, and obtain a data set containing de-identified records of patients treated by a physician who served in GIM during the SCRIPT intervention period. In this way we will be able to determine the CTT where a patient received treatment.

The readmission dataset will be constructed with criteria similar to van Walraven et al. [20]. Patients will be identified as eligible for the readmission pool if they had a nonelective admission to one of the participating sites' GIM divisions through its medical or surgical department, were discharged alive from the participating site's GIM division in the same index admission, and had a nonelective medical or surgical readmission to any Ontario hospital within either 7 days or 30 days of discharge of the index admission. Patients will be excluded if they were admitted from or discharged to another hospital in the index admission; if they had no patient identifier or an invalid identifier; if they lacked key information; or if they exceeded the 99^th ^percentile of distributions of the following variables for all Ontario hospitals: hospital length of stay, number of previous hospitalizations, number of follow-up visits, or case resource consumption.

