Implementation will be augmented in the following ways. First, we will establish a broad network of core "faculty advocates" in the intervention teams. Advocates will act as role models and provide direct verbal instruction to their colleagues on the team. We will ask the Patient Care Managers (or equivalents) on intervention teams to enlist the support of staff members who are willing to champion the intervention. Second, advocates will receive initial training about the intervention etiquette from research staff. Third, researchers will provide consultation to advocates to support them in the training, implementation, and uptake goals. Finally, we will use email as a delivery channel to inform advocates of the latest research results and to offer suggestions for reinforcement throughout the duration of the study. The responsibility for implementation of the intervention therefore is shared by researchers and staff-participants in GIM. We anticipate that these combined initiatives will promote increased buy-in and uptake among front line staff-participants in the GIM experimental teams.

In each intervention CTT we expect that thirty minutes will be required to explain the intervention to professional leaders and to field questions. We expect it will take ten minutes of discussion by each of the professional leaders with their trainee or reporting colleagues in each profession. We expect that the time cost of reinforcement will be fleeting, and might occur two or three times per week, at such times as regular rounds or meetings within professions, in interprofessional team meetings, in individual supervision and education meetings, and in opportunistic conversations.

The intervention will run approximately eight weeks in the intervention CTTs. In this time it will expose two rotations of staff and resident physicians and the other health professional staff with whom they work on the teams to the communication and collaboration script. At each hospital site, staff and patient outcomes related to each of the two intervention and control health care teams will be compared.

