### Randomization

#### Sequence generation

The trial is a cluster randomized trial. Stratification is by hospital site. Each stratum has exactly four GIM clinical teaching teams. In five hospital sites, each of four GIM clinical teaching teams will be randomized to intervention or control group status using numbers generated at random by the web site [28], a website service for generating random numbers. Two clinical teaching teams will be intervention teams; two others will be control teams. Assignment of teams is not performed in 'batch mode.' In other words, each unique hospital site's four teams will be assigned a group status with just a few months' lead time, usually after the conclusion of the intervention period at a previous site.

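### The patient-to-team link uses no rotation dates, so patients of a physician who changes team may be counted in the wrong arm

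*Protocol article*

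**What the plan says.** The protocol article describes the link in Outcomes: measurement, Readmission data:

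- Team membership comes from the divisions: "Leaders of GIM divisions will provide us with the names and team assignments of physicians who were on rotation in GIM CTTs during SCRIPT's intervention".
- Names are converted to registration numbers, which form the join: "Physicians' CPSO registration numbers will serve as the link between their positions in GIM CTTs and discharge information in the DAD".
- The list of numbers goes to the data holder, which returns "records of patients treated by a physician who served in GIM during the SCRIPT intervention period".
- The section treats this as sufficient: "In this way we will be able to determine the CTT where a patient received treatment".

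Length of stay data says that length of stay is built by the same process.

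Three other places bear on whether one physician means one team:

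- Intervention, on the roughly eight-week period: "In this time it will expose two rotations of staff and resident physicians".
- Sequence generation, on each hospital's four teams: "Two clinical teaching teams will be intervention teams; two others will be control teams".
- Statistical methods, Readmission: the analysed discharges run from one week after the intervention starts to one month after it ends.

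**The concern.** A list that pairs each registration number with a team identifies the treating team only if every physician stays on one team for as long as discharges are counted. The design does not secure that. Attending physicians change at least once within the intervention period, and the alternative teams in the same hospital include teams in the other arm. With two rotations in about eight weeks, the extra month of discharges is roughly one further rotation. The list is described as covering the intervention periods only, so a listed physician who moved in that month would still be tied to the earlier team.

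The protocol anticipates similar crossings elsewhere. Patients readmitted to another team count only by their first admission (Statistical methods, Readmission). Nurses and other health professionals who work across arms name their main team (Collaboration survey data). Physicians, whose number is the linkage key, have no such rule.

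The link fixes the arm for the primary outcome and for length of stay. If the intervention works, patients counted in the wrong arm make the two arms look more alike. A null result would then be harder to interpret.

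**Working it through.** **Inputs** (Sample size and Sequence generation): 20 teams, 10 per arm; 200 patients per team; about 4000 in total; intracluster correlation 0.01; 10% versus 5% readmission; significance 0.05, taken as two-sided; stated power 93%. Second scenario: 5% versus 2.5%, stated power 67%.

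**Reproducing the plan's figure.** The design effect is 1 + (200 − 1) × 0.01 = 2.99. The effective number per arm is 10 × 200 / 2.99 = 668.9. With p̄ the mean of the two rates,

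power = Φ{ [ |p1 − p2| − 1.96 √(2p̄(1 − p̄)/n) ] / √( (p1(1 − p1) + p2(1 − p2))/n ) }.

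For 10% versus 5%: (0.05 − 1.96 × 0.01440) / 0.01434 = 1.52, so power is 93.6%. For 5% versus 2.5% it is 67.3%. Both agree with the protocol, so the sample size calculation is not in question.

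**What one crossing physician does.** Assume one attending per team per rotation and equal patient numbers in each such block, and ignore the extra month of discharges.

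- A site has 4 teams × 2 rotations = 8 blocks of 200 / 2 = 100 patients.
- A physician with one block in each arm, tied to a single team, puts one block in the wrong arm. That is 100 / 800 = 12.5% of the site and 100 / 4000 = 2.5% of the trial.

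**Effect on the difference.** If a share f of each arm's patients really belongs to the other arm, the expected rates are p1 − f(p1 − p2) and p2 + f(p1 − p2). The difference is therefore multiplied by (1 − 2f).

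| Assumed f, whole trial, balanced | Difference (10% v 5%) | Power | Power (5% v 2.5%) |
|---|---|---|---|
| 0 | 5.0 points | 93.6% | 67.3% |
| 2.5% | 4.75 points | 91.0% | 62.8% |
| 5% | 4.5 points | 87.9% | 58.2% |
| 10% | 4.0 points | 79.4% | 48.6% |

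**When the error runs one way.** A single crossing physician moves patients in one direction only. Suppose 100 intervention patients are labelled control. The control rate becomes (2000 × 0.10 + 100 × 0.05) / 2100 = 205 / 2100 = 9.76%, the intervention rate stays at 5%, and the difference is 4.76 points. That is close to the 4.75 points of the balanced case, so the balanced figures serve as a guide at this size.

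The shares f are assumptions. No figure in the protocol says how many physicians move between teams.

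**The case against.** The strongest reply is that team does not come from the number by itself. It comes from the division leaders' assignments, and the number only joins that list to the discharge record. The list might carry dates, and the discharge database holds them: "Data in the DAD can be used to identify dates of index hospital admissions and, subsequently, readmissions". Research staff know the allocation, so a physician listed on two teams could be noticed when the list is compiled. The records returned for listed physicians are only an extract, later narrowed by the eligibility rules, the discharge window and the first-admission rule. A condensed article may also leave linkage detail to a fuller document.

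Most of this stands as a limit on the point. The means to resolve a move may well be at hand. But the article does more than stay silent: it sets out the steps, includes no date in them, and says that they determine the team. The narrowing rules do not help either, because none of them deals with a physician who moves.

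A reader might infer that patients are in fact being misassigned. The documents do not support that. Two rotations make a physician's move between arms possible, but nothing says that one occurred. A reader might also take the 12.5% as a trial-wide share. That would need one such physician at every site, each tied to a single team; one physician at one site gives 2.5%.

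**Conclusion.** The concern holds in a limited form. As written, the link is safe only if each physician keeps one team throughout the discharge window. The protocol gives no assurance of that, and its rotations, its within-hospital randomization and its longer discharge window all make an exception plausible. The outcomes exposed are readmission and length of stay, and the expected direction of error is towards no difference.

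The size cannot be derived from the documents. Under the assumptions shown, one crossing physician in the whole trial costs little: about 2.5% of patients, with power near 91%. The loss becomes material only if crossings recur. A balanced 10% share would leave about 79% power for 10% versus 5%. The point is worth acting on because the remedy is cheap and can be settled before the data are released.

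**What to change.** Ask each division for a roster with start and end dates for every physician on every team, covering the whole discharge window and not only the intervention period. Assign each index admission by registration number, hospital and date.

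Set one date rule in advance for stays that span a rotation change, for example the team rostered on the discharge date. Keep all such patients in the main analysis, in line with the intention-to-treat comparison, and add a sensitivity analysis that leaves out ambiguous links. Dropping these patients from the main analysis would sit badly with that principle.

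The cost is slightly more roster and linkage work: dates added to a list the divisions already supply, matched to dates the discharge database already holds. No extra patients are needed.

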#### Length of stay data

Development of data for analysis of patients' length of stay is identical to the process for readmission data. Length of stay will be calculated as the number of days between the dates of the start and end of each admission. If both dates are the same then the length of stay will be 0 days.

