### Sample size

Sample size and power were estimated with PASS software [27]. The trial's primary outcome is the proportion of unplanned hospital readmissions among patients discharged from a GIM team. We assume an intracluster correlation coefficient of 0.01. In this trial we expect there will be in excess of 200 patients admitted into each clinical teaching team in the 2-month intervention period. In total there will about 4000 patients admitted into and discharged from twenty clusters (teams) over five hospital sites. We assume that a typical rate of readmission among GIM patients within 30 days after discharge is ten percent. When significance is set at p < 0.05, the trial would have 93% power to detect a 5.0 percentage-point lower rate of unplanned hospital readmission among patients discharged from intervention CTTs than control CTTs (i.e., 10% versus 5%). A 5.0 percentage-point difference would represent a fifty-percent difference in readmission rates between intervention and control team patients.

If the rate of readmission within 30 days of discharge from GIM treatment is five percent, and if the intracluster correlation coefficient is 0.01, then the trial has 67% power to detect a 2.5 percentage-point lower rate of readmission among patients discharged from intervention teams. Again, this is a fifty-percent difference (i.e., 5% versus 2.5%).

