#### Readmission

Two patient follow-up periods will be investigated for unplanned hospital readmission: the primary outcome, 30 days post-discharge, and a secondary outcome period of seven days post-discharge. Discharge records will be examined for patients discharged to home between one week after intervention period commencement and one month after intervention conclusion. Readmission proportions will be calculated for patients discharged from intervention and control group teams. The significance of the difference in proportions will be tested with chi-square and association statistics adjusted for the cluster randomized design [29-32]. The primary aim of the trial is to estimate the population-level intervention effect on binary-coded readmission outcomes; consequently, generalized estimating equations will be employed to control for clustering.

Some patients could have multiple hospital admissions, possibly to different hospitals during the study period. Furthermore, some of the admissions may qualify as an "outcome" while others do not. This situation raises a possibility that patients could change clusters (teams) during the trial, by being readmitted to a different GIM team within the same hospital that discharged them earlier in the intervention period. Therefore, a patient will contribute an observation to the analysis only from their first admission during the intervention period. If the readmission is to a different hospital than the index admission, then the readmission is 'credited' to the hospital of the index admission.

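### The eligibility rule for the readmission dataset includes the primary outcome itself, which contradicts the plan's own denominator of all patients the teams discharge

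*Protocol article*

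**What the plan says.** All references are to the protocol article.

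- **Readmission data, inclusion.** The section opens its criteria with "The readmission dataset will be constructed with criteria similar to" those of a cited study. It continues: "Patients will be identified as eligible for the readmission pool if they had a nonelective admission to one of the participating sites' GIM divisions". Live discharge from the same admission is added, and then, joined by the word and, that the patient "had a nonelective medical or surgical readmission to any Ontario hospital within either 7 days or 30 days of discharge of the index admission".
- **Readmission data, exclusions.** A separate sentence removes transfers in or out at the index admission, missing or invalid identifiers, missing key information, and values above the 99th percentile for length of stay, previous hospitalizations, follow-up visits or resource consumption.
- **Readmission data, data request.** Earlier in the section, the plan is to "obtain a data set containing de-identified records of patients treated by a physician who served in GIM during the SCRIPT intervention period". That is not limited to readmitted patients.
- **Sample size.** The primary outcome is "the proportion of unplanned hospital readmissions among patients discharged from a GIM team", powered on about 4000 patients.
- **Statistical methods, Readmission.** "Readmission proportions will be calculated for patients discharged from intervention and control group teams". Readmission is coded as binary and analysed with generalized estimating equations. Each patient contributes only the first admission in the intervention period, and the discharges examined are those to home.
- **Length of stay data.** Development of data for "length of stay is identical to the process for readmission data".
- **Statistical methods, Length of stay.** Means are compared between patients whom the intervention and control teams discharged, with no mention of readmission.

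**The concern.** The inclusion list mixes two things: who is at risk of a readmission, and who had one. A binary analysis needs patients coded 0, but the list admits only patients coded 1. It is the only set of inclusion criteria given for the dataset that carries the primary outcome, so an analyst who builds the file from it would drop every non-event.

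If the pool is instead read as the set of events, a different gap opens. The exclusions follow directly on the definition of the pool, and nothing says that they also apply to discharged patients who were not readmitted.

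The length-of-stay section refers back to the same process. If that includes the inclusion list, length of stay would be compared only among readmitted patients. They would be selected on an event after randomization that the intervention is meant to reduce, and randomization would no longer protect that comparison.

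**Working it through.** **1. Which denominator does the stated power use?**

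Inputs from Sample size and Randomization: five sites with two intervention and two control teams each, so 10 teams per arm; about 200 patients per team, so 2000 per arm and 4000 in total; intracluster correlation 0.01; significance level 0.05, sidedness not stated; rates 10% versus 5%, and 5% versus 2.5%.

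- Design effect = 1 + (200 − 1) × 0.01 = 2.99.
- Effective n per arm = 2000 / 2.99 = 668.9.
- Power = Φ[(p1 − p2 − 1.96 × SE0) / SE1], with SE0 = √(2p̄(1 − p̄)/n), p̄ the mean of p1 and p2, and SE1 = √((p1(1 − p1) + p2(1 − p2))/n).

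| Method | 10% vs 5% (stated 93%) | 5% vs 2.5% (stated 67%) |
|---|---|---|
| Two-sided normal test, pooled | 93.6% | 67.3% |
| Two-sided normal test, unpooled | 93.7% | 67.4% |
| Two-sided, continuity-corrected | 92.1% | 61.9% |
| One-sided normal test, pooled | 96.7% | 77.7% |
| Two-sided t, 18 df | 90.9% | 62.6% |

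Of these, only the two-sided normal test without continuity correction matches both stated figures. It uses 2000 discharged patients per arm, so the sample size treats all discharges as the denominator.

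**2. What would the inclusion list give if followed literally?**

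- At 10% vs 5%: 0.10 × 2000 = 200 control and 0.05 × 2000 = 100 intervention patients. That is 300 of 4000, or 7.5%.
- At 5% vs 2.5%: 0.05 × 2000 = 100 and 0.025 × 2000 = 50. That is 150 of 4000, or 3.75%.

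With the 30-day outcome, every patient in such a file is an event. The proportion is 100% in both arms by construction, and there is nothing to test.

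**3. What if the pool is only the numerator?**

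The size of the mismatch depends on the share of readmitted patients that the exclusions remove, which the document does not give. Assume, for illustration only, 5% to 20%, with nobody removed from the denominator. A true 10% would then appear as 0.10 × 0.95 = 9.5% down to 0.10 × 0.80 = 8.0%.

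**4. Does length of stay inherit the restriction?**

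The Length of stay data section points to the readmission process. That process has two parts: linking patients to teams through physician registration numbers, and then the inclusion and exclusion list. If both are meant, the length-of-stay comparison shrinks to the 300 or 150 patients in step 2. If only the linkage is meant, it does not. Statistical methods names the patients discharged by the teams, which fits the second reading.

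**The case against.** A reader might infer that the trial has no valid denominator for its primary outcome. The document as a whole does not support that. The first hypothesis, the data request, Sample size and Statistical methods all refer to the teams' patients or discharges generally. The analysis section also says that some admissions count as outcomes and others do not, so non-events are plainly expected. The word pool can be read as the event set.

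A reader might also infer that length of stay will certainly be analysed in readmitted patients only. That does not follow either. Process may mean only the physician-number linkage, and both the third hypothesis and the length-of-stay analysis paragraph describe patients without regard to readmission.

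The numerator mismatch is likewise an inference. The exclusions stand in their own sentence, the transfer exclusion is tied to the index admission, and nothing limits them to readmitted patients. A condensed article may leave such detail to the full protocol.

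All of this stands, and it limits the point to an internal contradiction. It does not remove the contradiction. The inclusion sentence is a stated rule, not an omitted detail, and it gives an unusable file if followed. The right cohort can be recovered only by overruling that sentence with other sections.

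**Conclusion.** The Readmission data section wrongly makes the primary outcome a condition of eligibility. That conflicts with its own data request, with Sample size and with the readmission analysis. The evidence that all discharged patients were intended is strong, including the stated power, which reproduces on 2000 per arm.

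The figures of 300 (7.5%) and 150 (3.75%) patients show what the literal rule would leave. They assume about 4000 patients and the full hypothesized halving of readmissions. They do not estimate bias in the trial as otherwise described.

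Two consequences remain open ambiguities: whether the exclusions cover the denominator, and whether length of stay is restricted in the same way. A third mismatch belongs with them: the dataset requires live discharge, whereas the analysis section examines discharges to home.

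**What to change.** Split the inclusion sentence in Readmission data into two definitions.

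- **(a) Index cohort, the same for both arms.** The first nonelective GIM admission to a participating team, with live discharge. Apply the exclusions alike to patients with and without a readmission.
- **(b) Outcome.** Nonelective medical or surgical readmission to any Ontario hospital within 30 days of index discharge (secondary: 7 days), coded 0/1 for every member of cohort (a).

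Then:

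- Have the Length of stay data section refer to cohort (a).
- Reconcile the live-discharge criterion with the discharged-to-home restriction in Statistical methods, so that one population is named throughout.
- Do not describe the 99th-percentile exclusions as baseline criteria. Length of stay is itself a trial outcome, and follow-up visits and resource use may also arise after randomization.

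The cost is a rewording of these sections and of the file specification. The planned request already covers all patients of the listed physicians, so no new data are needed. The sample size and the stated 93% and 67% power are unchanged, because they already rest on all discharged patients.

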### Objectives: hypotheses

The SCRIPT Programme aims to create a cultural shift in the way health professionals communicate and collaborate in GIM hospital teams. There are three objectives for the SCRIPT Programme, the first two of which have been successfully completed. They are:

1. To assess interprofessional communication and collaboration;

2. To create an intervention – a tool or other process – that improves interprofessional communication and collaboration;

3. To implement and evaluate the effects of the intervention on outcomes.

The objective of the trial is to implement and evaluate the effects of an intervention aimed at enhancing collaborative communication between professionals and improving patient-centred care.

The research hypotheses for trial-related quantitative outcomes are:

1. Patients who are discharged from intervention teams will be less likely to be readmitted to hospital than patients discharged from control teams;

2. Mean time to readmission will be longer for patients discharged from intervention teams than for patients discharged from control teams;

3. Patients who are cared for by intervention teams will have shorter mean lengths of stay than patients in control teams;

4. Survey-measured perceptions of interprofessional collaboration will be higher among staff members of intervention teams than staff members of control teams;

5. Patients will report higher satisfaction with care after being treated by intervention teams than by control teams;

6. There will be an association between the number of calls to staff members' paging devices and team status; intervention-team staff members will receive fewer pages;

7. Adherence rates to evidence-based best practices for prescription drug therapy of geriatric acute-care inpatients will be greater among intervention teams than control teams.

Qualitative data are not collected in confirmation or denial of a hypothesis, but in explanation of the findings of the intervention trial. These data will be used to understand staff perceptions of the effects of the intervention and the barriers and catalysts for its implementation.

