### Statistical methods

Team and patient outcomes will be compared on an intent-to-treat basis.

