#### Length of stay

Mean lengths of stay will be compared between patients discharged from intervention and control group CTTs. Intervention group effects will be estimated with linear mixed models.

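### The 99th-percentile exclusions drop patients on variables that arise after randomisation and, as written, truncate the length-of-stay outcome on its own value

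*Protocol article*

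**What the plan says.** All references are to the protocol article.

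- **Outcomes: measurement, Readmission data.** Patients are excluded if they exceed the 99th "percentile of distributions of the following variables for all Ontario hospitals". The variables are "hospital length of stay, number of previous hospitalizations, number of follow-up visits, or case resource consumption".
- **Outcomes: measurement, Length of stay data.** "Development of data for analysis of patients' length of stay is identical to the process for readmission data". Nothing there exempts length of stay from the trim.
- **Objectives: hypotheses.** Hypothesis 3: "Patients who are cared for by intervention teams will have shorter mean lengths of stay than patients in control teams".
- **Statistical methods, opening sentence.** "Team and patient outcomes will be compared on an intent-to-treat basis".
- **Statistical methods, Length of stay.** "Mean lengths of stay will be compared between patients discharged from intervention and control group CTTs", using linear mixed models. No untrimmed analysis is described.
- **Randomization, Sequence generation.** "each unique hospital site's four teams will be assigned a group status with just a few months' lead time". Allocation therefore precedes the index stays.
- **Statistical methods, Readmission.** Records are limited to discharges home from one week after the intervention starts to one month after it ends. Only a patient's first admission in the intervention period counts.

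**The concern.** Of the four trimming variables, only the number of previous hospitalisations clearly precedes the care under test. Length of stay is a trial outcome, and resource consumption belongs to the same stay. The article does not define follow-up visits; on the plain wording they come after discharge and may overlap the readmission window.

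The cut-point is fixed and external, so it need not remove the same share of each arm. If the intervention shortens stays, some patients who would have been above the cut fall below it and enter the intervention mean as long stays, while their control counterparts are deleted. A real reduction in mean stay then looks smaller than it is. Hypothesis 3 would be tested on a sample selected by its own outcome, and a null result would be hard to interpret. The readmission set is also conditioned on variables that the intervention could change, which does not fit an intent-to-treat comparison.

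**Working it through.** **1. The plan's own figures.** Inputs from Sample size: 10 teams of 200 per arm, ICC 0.01, alpha 0.05 (taken as two-sided).

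Design effect = 1 + 199 × 0.01 = 2.99. Effective n per arm = 2000 / 2.99 = 668.9. Power = Φ[(d − 1.96·SE0) / SE1], with SE0 from the pooled proportion and SE1 from the two separate ones.

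- 10% v 5%: (0.05 − 1.96 × 0.01440) / 0.01434 = 1.52, power 93.6% (stated 93%).
- 5% v 2.5%: (0.025 − 1.96 × 0.01039) / 0.01037 = 0.45, power 67.3% (stated 67%).

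Both reproduce. Losing 1–4% of patients to the trims leaves 93.5–93.3% and 67.1–66.7%, so power is not the issue.

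**2. Trim alone, proportional effect.** The article gives no length-of-stay distribution. Assumed: log-normal stays, control stays distributed like the Ontario reference, and a true 10% cut in every stay. With a = (ln c − μ)/σ, the mean below cut c is exp(μ + σ²/2) · Φ(a − σ) / Φ(a).

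Worked case, median 5, σ = 1.0: c = 5 · exp(2.326) = 51.2 days and the untrimmed mean is 8.24. The trimmed control mean is 8.244 × 0.9076 / 0.99 = 7.56. For intervention, a = 2.326 + 0.105 = 2.432, and the trimmed mean is 7.420 × 0.9239 / 0.9925 = 6.91. The difference is 0.65 days against a true 0.82, so 79% is kept.

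| Median, log-SD | Cut (days) | Bed-days above cut | True difference | Trimmed difference | Kept | Excluded, control v intervention |
|---|---|---|---|---|---|---|
| 5, 1.0 | 51.2 | 9% | 0.82 | 0.65 | 79.0% | 1.00% v 0.75% |
| 5, 1.2 | 81.5 | 13% | 1.03 | 0.76 | 73.5% | 1.00% v 0.79% |
| 6, 0.9 | 48.7 | 8% | 0.90 | 0.73 | 81.5% | 1.00% v 0.73% |

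Per 2000 patients that is 20 control exclusions against about 15 or 16 intervention exclusions.

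**3. Adding the discharge window.** Assumed: admissions uniform over 56 days (the article's approximate eight weeks) and discharge between day 7 and day 86 (56 + 30). Simulating the same three cases in the same order:

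- Window alone keeps 81%, 62% and 84% of the proportional effect.
- Adding the trim keeps about 94%, 100% and 94% of what the window leaves, a further loss of about 0–6%.

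With log-SD 1.2 the cut lies near 82 days, where the window has already removed almost every such stay.

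**4. Benefit concentrated in long stays.** Assumed: 30% off the excess over the 90th percentile. The trim alone keeps about 12–17% of the effect. With the window in place, the trim still removes most of what remains in two of the three cases. In the third (log-SD 1.2) the window alone already gives the wrong sign.

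**5. Primary outcome.** Assumed: no true effect, 10% readmission overall, excluded share e, readmission rate r among the excluded. The rate in those kept is (0.10 − e·r) / (1 − e).

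- Largest case, r = 0.40, e = 4% v 3%: 0.084/0.96 = 8.75% v 0.088/0.97 = 9.07%, a spurious 0.32 points.
- Smallest case, r = 0.20, e = 1% v 0.75%: 0.098/0.99 = 9.90% v 0.0985/0.9925 = 9.92%, about 0.03 points.

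The planned effect is 5 points.

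**The case against.** **The identical process may mean record linkage only.** Read to the letter, it would also carry over the condition that patients had been readmitted, which makes no sense for length of stay. It may therefore refer only to linking patients to teams through physician registration numbers. This is a fair point and makes the text ambiguous. But the sentence carries no such limit, and the linkage and the exclusions stand under the same heading. The readmission set is trimmed on either reading.

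**The design already truncates long stays.** This stands in part. The discharge window is stated under the readmission analysis; if it also governs length of stay, the 73–82% cannot be charged to the trim, and deleting the trim would not recover all of the loss.

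**The effect might be said to change sign.** A reader might infer this, because with the tail-only effect and 2% of general internal medicine patients above the provincial cut, the trimmed difference in one case is −0.06 days instead of +0.42. The documents do not support it. They give no share of these patients above the cut, and the intervention is a general protocol for face-to-face interactions about patients, not one aimed at long stays. Under the proportional effect, none of the cases reverses.

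**The criteria follow a published study.** The article says only that they are similar. Their origin does not settle whether they suit a randomised comparison.

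**Conclusion.** The concern holds in limited form. As written, the article removes patients from the length-of-stay comparison because of their length of stay, and from both comparisons on variables that arise after teams are randomised. That conflicts with its intent-to-treat statement.

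The size rests on assumed log-normal stays: the trim alone keeps about 73–82% of a 10% proportional reduction. If the discharge window applies as well, the trim's own further cost is about 0–6% for such an effect, and more if the benefit lies in long stays. The cut is external, so the true share removed is unknown.

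A reader might also infer that the primary result is seriously biased. The figures do not bear that out: 0.03–0.32 points under assumed inputs, with power almost unchanged. This should be fixed, chiefly for the sake of a secondary outcome.

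**What to change.** Under Readmission data, remove length of stay, follow-up visits and case resource consumption from the 99th-percentile exclusions for the main analysis sets of both readmission and length of stay. Under Length of stay data, state that all otherwise eligible index admissions are analysed, and say whether the discharge window applies. Report a trimmed or winsorised length-of-stay analysis as a sensitivity analysis only. The exclusion on previous hospitalisations precedes the care under test and may stay.

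The cost is an edit to one clause and a clarifying sentence, with no new data source. The variance of mean length of stay will be somewhat larger.
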